## Abstract

**Introduction:**

Psoriasis (PSO) is a disease that in the majority of patients is accompanied by itch, which imposes a great burden and positively relates to anxiety. *Social* anxiety, a facet of anxiety associated with social withdrawal, may be a predictor of itch intensity in this patient group. Moreover, anxiety is linked to the secretion of neuroendocrine and inflammatory parameters such as substance P (SP), interleukin (IL)-6 and IL-17, which are also related to itch. In this research project, we investigate first, whether there is a direct relationship between social anxiety and itch intensity in patients with PSO and second whether the secretion of SP, IL-6 and IL-17 in the skin mediates this relationship. Additionally, PSO-patients are compared to healthy skin controls regarding their level of social anxiety, itch intensity and the secretion of SP, IL-6 and IL-17.

**Methods and analyses:**

For study 1, we aim to recruit 250 psoriasis patients and 250 healthy skin controls who complete questionnaires to assess social anxiety, itch intensity and control variables (e.g. sociodemographic variables and severity of PSO). A linear hierarchic regression will be used to determine whether social anxiety significantly contributes to itch intensity. In study 2, we plan to apply the suction blister method to 128 patients and healthy skin controls recruited from study 1 to determine SP, IL-6 and IL-17 in tissue fluid extracted from the skin. A mediation analysis will be conducted using the SPSS-macro PROCESS to test whether the relationship between social anxiety and itch is mediated by SP, IL-6 and IL-17.

**Trial registration numbers:**

DRKS00023621 (study 1) and DRKS00023622 (study 2).

## Introduction

### Psoriasis (PSO) and itch, a self-reinforcing misalliance

PSO is a chronic inflammatory skin disease characterized by a hyperactivation of T-helper cell (TH) type 1 and 17 immune responses and related hyperproliferation of keratinocytes leading to visible skin lesions, especially at the elbows, scalp, lower legs and knees [1–4]. PSO affects about 2.5% of the German adult population and in the majority of patients it is accompanied by itch [5–9]. In fact, itch—in many cases—leading to scratching behavior [10] is regarded as the most bothersome symptom by PSO-patients [11]. This further impedes the patients’ appearance and in the following may lead to feelings of stigmatization, *social* anxiety and isolation, especially due to the stares of other people and negative self-assessment [12–14]. Closing a vicious circle, levels of internalized stigmatization have been shown to be related to PSO-severity and the visibility of lesional skin [14]. Overall, PSO often so dramatically impedes the well-being of the patients that PSO-patients show increased levels of depression and suicidal ideation compared to healthy controls [15–18].

### Itch links with psychological factors

Itch is related to a number of psychological factors including stress, personality traits, depression and self-consciousness [19–23]. In a mice model, it has been shown that social deprivation increased both, anxiety related behavior and self-scratching responses [24]. Other work demonstrates that acute [25] and chronic itch [26, 27] play an important role in triggering behavior, which reflects states of anxiety in mice. This effect seems to be associated with mast cell activation as mice that received injections of compound 48/80 after 10 days of water avoidance stress, showed increased scratching responses compared to a control group without stress induction [28]. Corresponding to these observations in mice, patients with dermatologic conditions who reported increased anxiety, also reported more severe itch, which in turn was aggravated by scratching behavior [29]. While scratching as response to induced itch was judged as relieving in skin healthy participants [30], PSO-patients perceive self-scratching due to disease related itch as burdening in various daily social situations [31], and show a positive relationship between anxiety and itch [32–34]. In turn, selective serotonin reuptake inhibitors reduce itch in dermatologic and psychosomatic patients [35], and giving escitalopram significantly diminishes anxiety levels and itch in PSO-patients with psychiatric disorders [36]. The above mentioned studies demonstrate the important role of the link between itch and anxiety in PSO-patients. Social anxiety represents a facet of anxiety that deserves special interest in this context. It is related to more severe psychological comorbidities such as depression and suicidality, which also play a role in psoriasis [15, 37–40]. Even though it has been shown that itch is linked to anxiety in patients with PSO and atopic dermatitis (AD) [11, 32, 41] the role of social anxiety has not been investigated in detail in PSO-patients.

### Neuroendocrine and inflammatory parameters relate to itch and anxiety

There are a number of neuroendocrine and inflammatory parameters interacting with each other, which are related both to the intensity of itch as well as to anxiety. Of these parameters, we consider substance P (SP), IL-6 and IL-17 of special interest. Concerning itch, injected SP was shown to induce it in mice [42, 43], in healthy human controls [44], as well as in PSO-patients [45]. Within this context, it was recently shown that in PSO-patients and in patients with atopic dermatitis, the amount of SP and its neurokinin-1 receptor (NK-1R) receptor was significantly increased in nerve fibers in itchy compared to non-itchy skin of the same patients and to healthy controls [46]. In the same study, gene fold changes of IL-6 and IL-17A were overexpressed in itchy skin of PSO-patients. Of note, SP is capable of liberating IL-6 and IL-17 [47, 48], and IL-17 has also been shown to further release IL-6 [49]. Moreover, higher levels of IL-6 have been found in itchy skin of patients with different diseases. With this respect, it was found that IL-6 concentration were significantly related to scratching behavior after intradermal injections of calcium phosphate in mice. In the same study, in human subjects with chronic kidney disease, IL-6 concentrations were significantly increased in itchy compared to non-itchy skin [50]. In addition, an increased amount of nerve fibers containing IL-6 was found in lesional compared to non-lesional skin of patients with the itchy skin diseases atopic dermatitis and prurigo nodularis [51]. More recently, this finding was supported by a positive relationship between pruritus severity and IL-6 in patients with prurigo nodularis [52]. In addition, IL-17-antagonists were shown to reduce itch in PSO-patients [53–55].

These neuroendocrine and inflammatory parameters are also associated with anxiety [56–61]. First of all, the availability of the NK-1 receptor in the amygdala was shown to be significantly associated with anxiety-like personality traits in healthy individuals [62]. Also, the induction of itch by intradermal injections of histamine, which can be liberated by SP [44], caused anxious behavior in mice [25]. Moreover, IL-6 has been shown to be significantly elevated in patients with clinically diagnosed anxiety disorder compared to non-anxious individuals [56]. Similarly, IL-17 concentrations were shown to be elevated in mononuclear blood cells of patients with generalized anxiety disorders compared to healthy controls [63]. In both groups, IL-17 levels significantly increased after SP was added to the cells in a concentration that mimicked a stressful event, which supports the biological link between anxiety, SP and inflammation.

Due to the known relationships between these parameters and anxiety on the one hand and itch on the other hand, the link between anxiety and PSO-itch could be mediated by SP, IL-6 and IL-17 [64]. In this study, we investigate whether social anxiety can predict itch and whether this relationship is mediated by the release of these neuroendocrine and inflammatory parameters. To study this interaction on the local stress mediator release level, we here plan to use a minimally invasive skin sampling technique, the suction blister method [65], which allows the determination of these neuroendocrine and inflammatory parameters directly in the epidermis and interstitial cutaneous fluid.

### Objectives

The first aim of the research project is to investigate whether social anxiety is a predictor of itch in PSO-patients (study 1). The second aim of this research project is to answer the question whether IL-6, IL-17 and SP mediate the relationship between social anxiety and itch intensity in PSO-patients. In addition, we investigate, whether healthy skin controls and PSO-patients differ regarding social anxiety and/ or the release of SP, IL-6 and IL-17 (study 2; also see spirit schedule, Fig 1)

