## Materials and methods

### Study design, patient recruitment, inclusion and exclusion criteria

Study 1 is a cross-sectional observational questionnaire study to answer the first research question (whether itch and social anxiety are related in PSO-patients) and to recruit PSO-patients willing to perform suction blister sampling for study 2. Study 2 is a controlled laboratory study, in which we plan to include a selected subpopulation of high and low socially anxious PSO-patients and healthy skin controls as described below. In order to recruit participants for study 1, PSO-patients will be informed about the study by written and oral announcements, information by their dermatologists as well as via websites of German psoriasis networks. Healthy skin controls will be recruited via oral and written announcements. In case patients/healthy skin controls are interested in participation in study 1, they will be contacted by staff from the Institute of Medical Psychology of the Justus-Liebig-University of Giessen via telephone, and receive further information on the study. During this telephone call, inclusion and exclusion criteria will be checked. In order to be included in study 1, participants need to be between 18–65 years old, know the German language well enough to be able to fill in the questionnaires adequately, and in case of PSO-patients have been clinically diagnosed with PSO at least six months prior to inclusion. PSO-patients and controls with other itchy (skin) conditions such as bullous disorders are excluded. Also, individuals who currently receive or have received psychotherapeutic/ psychopharmacological treatment due to a psychological/ psychiatric disorder during the last six months are excluded. Further exclusion criteria for study 2 are a diagnosis of any transmissible disease, and treatment with biologicals, because these can interfere with neuroendocrine and immune parameter measurements [66]. In general, we strictly protocol medical and psychological conditions before inclusion and at the beginning of the examination in order to be able to assess how comorbidities affect our findings.

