### Study procedure

The research project is divided into two studies. Study 1: After inclusion, validated self-report instruments and a consent form will be sent to the participants by mail, which they are to return to the Institute of Medical Psychology in pre-stamped envelopes provided with the package. The questionnaire sets include items to assess sociodemographic information, social anxiety and itch intensity. In case of PSO-patients participants will additionally report about the severity of their PSO. The data will be transferred to IBM® SPSS® and stored pseudonymously in line with the data protection regulations. For participation in study 1, participants are financially reimbursed. They are also asked to leave their contact details, if they are interested in participation in study 2.

Study 2: Patients and healthy skin controls will be selected from the pool of study 1, who showed interest to participate in study 2. They will be informed about the procedures involved in study 2 in a telephone conversation. In this phone call, the inclusion and exclusion criteria (see above) will be assessed. After inclusion, participants will be invited to the laboratory of the Institute of Medical Psychology. Participants will be habituated to the suction blister method by verbal instructions of the experimenter, and a demonstration of the loudness and handling of the suction pump (session 1; habituation). Participants are informed that they can withdraw from the study at any time without giving reasons. Afterwards, they give their informed consent and have a standardized lunch break before the actual induction of blisters on the skin (session 2). At the beginning of the second session in the laboratory, participants will be asked to fill in the same questionnaires as in study 1. In addition, in study 2, two further questionnaires will be deployed to assess the current psychological health, and current/ general anxiety and depression (see below). Afterwards, the suction blister pump will be used to induce blisters. This allows the collection of blister fluid and the roof of the blisters for determination of neuroendocrine and inflammatory parameters therein. In total, both sessions of study 2 will last 5.5 hours approximately. All participants will receive a financial compensation for participation in study 2. Details and unforeseen events during the trial will be protocolled by the experimenter.

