### Psychometric measures

#### 1) Social anxiety

Social anxiety is measured in both studies by means of the *social anxiety disorder scales* (SOZAS) [67]. These include the *social interaction anxiety scale* (SIAS) and the *social phobia scale* (SPS). Both are validated German questionnaires, which contain 20 items each that need to be answered on a 5-point scale. The SIAS measures interactional anxiety, the SPS measures anxiety in evaluation situations. The items in both questionnaires do not refer to a specific time period. In this research project, subjects will be categorized as being either high (HSA) or low (LSA) socially anxious according to a median split of the SIAS scores in order to determine whether these groups differ in itch intensity and the secretion of assessed neuroendocrine and inflammatory parameters.

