Separate analyses will be conducted for patients and controls. To determine the required sample size, we performed an analysis using G*Power [89] to extrapolate the sample size for study 2. Based on correlational studies regarding itch and anxiety [33] as well as on neuroinflammatory parameters and itch [52] in PSO-patients we expect small to medium sized effects (f^2^ = .10). The estimation with an α of 0.05 and a β of 20 revealed that 64 healthy skin controls and 64 PSO-patients are to be included in study 2. Small to moderate effects can be assumed because, on the one hand, only extreme groups are examined and, on the other hand, small to moderate correlations between anxiety and itch intensity (*r* = .179; *p* = .003) have been found in PSO-patients [33] and between neuroinflammatory parameters and itch intensity (*r* = .60; *p* < .01) [52]. In case, that patient recruitment for the studies is slower than anticipated, we would aim to gather additional personnel and material resources to improve the recruitment rate over time. Since study 2 has more strict inclusion and exclusion criteria on e.g. medication and comorbidities than study 1 (see inclusion and exclusion criteria), we expected a reduction in participants who match these premises. In addition, motivational factors are to be considered, as in contrast to study 1, study 2 will be conducted in a laboratory setting. We therefore estimated that n = 500 participants need to be included in study 1 to achieve the calculated sample size of n = 128 participants for study 2. As there is no cut-off value in the user manual of the SIAS [90] to categorize somebody as low socially anxious, we planned to use percent range ≤ 25 in order to categorize 32 participants per group as being low socially anxious. Due to the pandemic situation, participant recruitment during the course of 2020 and 2021 was and still is very difficult. Therefore, we had to change this inclusion criterion for study 2 and now invite all participants of study 1 irrespective of their social anxiety scores to take part in study 2. High and low socially anxious participants will now be identified by median split. Statistical analyses will be conducted when the targeted sample size (study 1: *N* = 500, study 2: *N* = 128) has been achieved or further inclusion of participants is no longer possible due to the end of funding. No intermediate data analysis is planned. Data collection started after ethic approval in December 2020 for study 1 (number of currently assessed patients n = 234; number of currently assessed healthy controls n = 174), and in September 2021 for study 2 (number of currently assessed patients n = 27; number of currently assessed healthy skin controls n = 15). Data collection will be continued until the planed sample sizes are reached or as long as funding is available.

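### The patient-control comparison of social anxiety is placed in study 2 (64 v 64), although study 1 collects the same scales in 250 v 250; using study 1 would halve the confidence interval at no cost

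*Protocol article*

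**What the plan says.** The Objectives label only the within-patient question, whether social anxiety predicts itch, as study 1. They then add the group comparison: "whether healthy skin controls and PSO-patients differ regarding social anxiety and/ or the release of SP, IL-6 and IL-17 (study 2". The legend to Fig 2 and the section on study design also give study 1 no group comparison.

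The abstract lists a patient-control comparison of social anxiety, itch intensity and the three mediators, but names no study for it. Statistical analyses describes no between-group test and says that patients and controls are analysed separately.

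On what is collected where:
- Study 1 (abstract, Methods and analyses): "we aim to recruit 250 psoriasis patients and 250 healthy skin controls who complete questionnaires to assess social anxiety, itch intensity and control variables".
- Study 2 (Statistical analyses): "64 healthy skin controls and 64 PSO-patients are to be included in study 2".
- Social anxiety (Psychometric measures): "Social anxiety is measured in both studies by means of the" SOZAS, that is, SIAS and SPS.
- Study 2 visit (Study procedure): "participants will be asked to fill in the same questionnaires as in study 1".

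Study 2 participants come from those in study 1 who expressed interest. They attend for about 5.5 hours, and transmissible disease and treatment with biologicals are further exclusions.

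**The concern.** Only SP, IL-6 and IL-17 need blister fluid. A comparison of SIAS and SPS between patients and controls needs only the mailed questionnaires, which study 1 collects from roughly four times as many people (500 v 128). Tying this objective to study 2 gives up half the available precision. A modest true difference in social anxiety could then go undetected while the data that would show it are already held.

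Study 2 is also a subset of study 1 after further filtering. Willingness to spend hours in a laboratory may depend on social anxiety itself, and the exclusion of biologicals would be expected to fall mainly on patients. If these filters act differently in the two groups, the difference in means is biased as well as imprecise.

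**Working it through.** **The plan's own figure.** The 64 per group comes from a G*Power calculation with f² = 0.10, α = 0.05 and a β given as 20, read here as 20%. For one regression coefficient with noncentrality √(f²·N), a one-sided test gives N = 64 (power 0.804), so the figure reproduces; a two-sided test would give N = 81. This sizes a regression within each group. It does not size a comparison between patients and controls.

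**Inputs for the comparison.** n = 64 v 64 (Statistical analyses) and 250 v 250 (abstract). The article gives no SD for SIAS or SPS, so results are in SD units. Tests are two-sided at 5%.

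**Confidence interval.** Half-width = t(0.975; 2n − 2) × √(2/n).
- Study 2: 1.979 × √(2/64) = 1.979 × 0.1768 = 0.350 SD.
- Study 1: 1.965 × √(2/250) = 1.965 × 0.0894 = 0.176 SD.
- Ratio: 0.350/0.176 = 1.99. With normal quantiles it is √(250/64) = 1.98. The SD cancels, so the ratio needs no assumption about it.

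**Detectable difference and power (two-sample t test).** The true difference is not given, so a range is assumed.

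| | 64 v 64 | 250 v 250 |
|---|---|---|
| Detectable with 80% power | 0.50 SD | 0.25 SD |
| Power at 0.2 SD | 20% | 61% |
| Power at 0.3 SD | 39% | 92% |
| Power at 0.4 SD | 61% | 99% |
| Power at 0.5 SD | 80% | over 99% |

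**At the study 1 counts already reported (234 v 174).** The half-width is 0.197 SD. A complete study 2 would still have an interval 1.77 times as wide: √(2/64) ÷ √(1/234 + 1/174) = 0.1768/0.1001.

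**Selection, by assumption only.** The planned uptake is 64/250 = 25.6% per group. Suppose the score is standard normal and attendance is logistic in it.
- If the log-odds of attending fall by 0.2 to 0.5 per SD in patients only, the patient mean shifts by about −0.15 to −0.36 SD, and the group difference with it.
- If the slopes are 0.3 in patients and 0.2 in controls, the difference shifts by about −0.07 SD.
- If the slopes and the score distributions are the same in both groups, the shift cancels.

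Nothing in the article favours one of these cases over another.

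**The case against.** The assignment rests on one parenthesis at the end of a paragraph. That parenthesis could be read as labelling the mediation aim just before it, which otherwise has no label, and it points to a schedule figure that is not shown. The abstract states the comparison for the whole project, nothing forbids using study 1 data, and a condensed article may leave the between-group test to a fuller plan. This lowers the certainty about intent. It does not change the natural reading of the sentence, and no other section moves the comparison to study 1.

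A reader might infer more: that study 2 is selected on SIAS itself, so the comparison is directly distorted and could even come out with the wrong sign. The design section does speak of "we plan to include a selected subpopulation of high and low socially anxious PSO-patients and healthy skin controls". Statistical analyses, however, reports that the percentile criterion was dropped, that all study 1 participants are now invited whatever their score, and that high and low groups are formed by median split. Selection on the score is therefore not a current source of bias, and a wrong sign would be speculation.

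Two other tempting arguments are weak. The interim study 2 counts (27 v 15) should not be used to judge power or uptake, because no intermediate analysis is planned and recruitment continues. Completing the scales after the pump demonstration is poor evidence of bias, since the items refer to no specific period and both groups follow the same procedure.

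It is also fair to say that this is an additional objective, and that the prediction and mediation aims in patients are unaffected.

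**Conclusion.** The point holds as one of efficiency, with a secondary risk of selection. As the Objectives read, the patient-control comparison of social anxiety uses a sample whose confidence interval is about twice as wide as the one available in study 1, and whose detectable difference is 0.50 rather than 0.25 SD. These figures assume that the target sizes are reached, a two-sided 5% test and a common SD. The power of 39% v 92% further assumes a true difference of 0.3 SD.

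The second selection step is documented, but a resulting bias is not. It would require selection to act differently in patients and controls, and the shifts worked out above are illustrations, not estimates. Study 1 participants are volunteers too, so using study 1 removes the second step and not all selection.

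**What to change.** In the Objectives and in Statistical analyses, name the study 1 sample as the primary basis for the patient-control comparison of SIAS and SPS. Do the same for itch intensity, for which the abstract names no study. Keep only SP, IL-6 and IL-17 in the study 2 patient-control comparison. Study 2 SIAS and SPS scores can still be reported descriptively, to show whether the groups whose mediators are compared also differ in social anxiety.

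The cost is a change of wording. The data are already being collected, no visit or participant is added, and since no intermediate analysis is planned the change can be made before any data are analysed.
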